### Research Governance

Three formal groups meet regularly to manage the trial within the SHIELD programme: the Project Management Group (PMG); the Programme Steering Committee (PSC); and the Data Monitoring and Ethics Committee (DMEC).

### Ethical arrangements

Ethical approval was given by the Outer North East London Research Ethics Committee (09/H0701/54). In line with Good Clinical Practice, we developed a Standard Operating Procedure for accurate and timely reporting of Serious Adverse Events to the Chief Investigator. He assesses whether either intervention could have caused each event and, if so, reports to the DMEC as appropriate.

#### Consent

The main participants are family carers and it is hoped that their relatives with dementia will also take part. They each enter the trial only after giving informed consent. We explain the nature of the research to all participants and give them at least 24 hours to consider the study information before seeking consent, stressing that their care will not change if they choose not to participate. We also tell the general practitioners (GPs) of all participants about their participation. If a person with dementia is considered to lack capacity, research staff, acting in accordance with the Mental Capacity Act 2005 [49] and the British Psychological Society Code of Ethics and Conduct [50], seek documented assent from the family carer. CSs also give informed consent as an acknowledgement of the CSs' Code of Conduct and also because they are participants in a linked project evaluating the impact of volunteering on the volunteer.

### Data management and statistical analysis

Data are entered into Infermed's MACRO™ Electronic Data Capture system for clinical trials that allows data to be both entered and reviewed. Data are managed within MACRO™ and exported to a statistical software package for analysis. Multiple imputation with a linear regression model will be used for imputing missing outcome data.

#### Effectiveness analysis

After exporting data to the statistical package SPSS, we shall follow the general approach of the UK BEAM trial [51] and analyse relevant outcomes on the basis of treatment allocated to test whether:

A. CSP, alone or in combination with RYCT, affected family carers and their relatives;

B. RYCT, alone or in combination with CSP, affected family carers and their relatives;

C. CSP and RYCT interacted in their effects on these outcomes.

Specifically we shall use multi-level analysis of covariance with outcome at 12 months after initial randomisation as dependent variable and 'outcome' at baseline and length of time on CSP as covariates, to compare: (A) CSP and combined groups with TAU and RYCT groups; (B) RYCT and combined groups with TAU and CSP groups; and (C) combined and TAU groups with CSP and RYCT groups. We shall also use linear mixed models to study longitudinal effects at 5 and 12 months. We shall treat RYCT versus TAU and CSP versus TAU as fixed effects, together with gender and dyad relationship. We shall treat the effects of locality (including personnel) and time as random effects and assess the covariance structure of this. We shall undertake sensitivity analysis to test whether plausible changes in key variables such as carers' ages and relationships to their relatives with dementia would have affected findings.

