## Design

The trial is a 2 × 2 factorial single-blind RCT (Figure 1): the 4 arms of the trial are CSP alone, RYCT alone, CSP and RYCT combined, and treatment as usual (TAU). To ensure enough participants to run viable RYCT groups, we randomise between TAU, RYCT, CSP and combined in the proportions 1:2:1:2. We collect data at baseline (post-consent, pre-randomisation), and 5 and 12 months after the first randomisation, with the main endpoint at 12 months. After randomisation, all participants are free to continue to receive treatment as usual from statutory and voluntary services in their locality. We conducted a feasibility study before the full RCT in accordance with MRC guidance on complex interventions guidance [21].

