### Randomisation

We use a two-stage sequential dynamic algorithm to allocate individual and group based interventions. We base the probability of choosing each group on the participants' stratification variables and the previous allocations for those variables. For the first allocation between CSP and TAU the stratification variables are locality and dyad relationship. In the latter, dyads are designated 'horizontal' or 'vertical' kinship, where horizontal denotes spouses and siblings and vertical denotes daughters, sons, daughters-in-law and other similar kinships where there carer and person with dementia are from different generations within the family. For the second allocation between RYCT and TAU we add the first allocation as a stratification variable to keep the four treatment arms in balance.

The SHIELD administrator enters participants' variables into a remote web-based randomisation, which then allocates them in equal proportions between CSP or TAU on an individual basis. Once adequate dyads have been randomised within each site (target 24; range 16-30), the remote randomisation system allocates them in a second randomisation between RYCT and TAU in the proportion 2:1 on a group basis. Hence the combination of these two randomisation stages results in results in the allocation between TAU, RYCT, CSP, and RYCT plus CSP in the proportions 1:2:1:2. The (unblinded) SHIELD administrator then informs carers of their allocation by letter, and liaises with the RYCT Facilitator and/or CS Coordinator as appropriate.

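### The 12-month model adjusts for time on CSP, which arises only after randomisation, so contrast A need not estimate the effect of being allocated CSP

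*Protocol article*

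**What the plan says.** All references are to the protocol article.

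- **Effectiveness analysis** states the principle: "analyse relevant outcomes on the basis of treatment allocated". It then specifies a multi-level analysis of covariance of the 12-month outcome, with the baseline value of the outcome and "length of time on CSP as covariates". That model serves three contrasts: CSP, RYCT and their interaction. The CSP contrast is "A) CSP and combined groups with TAU and RYCT groups".
- **Design** fixes the timing. On baseline: "We collect data at baseline (post-consent, pre-randomisation". Follow-up is at "5 and 12 months after the first randomisation, with the main endpoint at 12 months".
- **Randomisation** makes CSP versus TAU the first allocation. RYCT is allocated later, by group: "Once adequate dyads have been randomised within each site (target 24; range 16-30".
- **Peer Support** has CSP start after a matching process and plans three months plus a further seven, ten in all. **Implementation of Interventions** treats the amount of intervention received as a measure of receipt.
- **Effectiveness analysis** also plans linear mixed models over 5 and 12 months, with CSP, RYCT, gender and dyad relationship as fixed effects. Time on CSP is not listed there.

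The article does not say what value the covariate takes for dyads not allocated CSP, or whether it is centred.

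**The concern.** A covariate in a comparison of randomised groups should be fixed before randomisation, or at least be unaffected by allocation. Time on CSP is neither. Baseline precedes randomisation, and the outcome is taken a fixed 12 months after the CSP allocation, so time since that allocation is the same for every dyad. What remains to vary is how soon a match was made, whether CSP was taken up and when it stopped.

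Outside the CSP and combined arms the variable can only be zero, so it is almost a second copy of the allocation indicator. Part or all of the CSP effect can pass into its slope. The CSP coefficient then answers a different question: what would the difference be for a carer allocated CSP who spent no time on it? At stake is the test of the first of the trial's three null hypotheses at its main endpoint.

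**Working it through.** **Inputs.** From Sample size: CSP effect 0.42 SD, 240 completing dyads, 5% significance (two-sided assumed). From Design: allocation 1:2:1:2, giving 40/80/40/80 and hence 120 with CSP against 120 without. Assumed, because the article does not give them: baseline correlation 0.5; time on CSP in the CSP arms with mean m = 8 and SD s = 3 months, cut off at 0 and 12; raw months, zero elsewhere.

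**1. The plan's own figure.** SE = √(1/120 + 1/120) = 0.129; 0.42/0.129 = 3.25; 3.25 − 1.96 = 1.29; power 90.2%. The stated figure of more than 90% for CSP reproduces, for a comparison by allocation without time on CSP.

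**2. With baseline outcome only.** SE = √(1 − 0.5²) × 0.129 = 0.112; 0.42/0.112 = 3.76; power about 96%.

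**3. What the coefficient becomes.** The slope c on time is identified only within the CSP arms. The CSP coefficient is then b = Δ − c·m, where Δ is the effect of allocation.
- Benefit unrelated to time: c = 0, b = 0.42.
- Half the benefit proportional to time: c = 0.21/8, b = 0.21.
- All of it proportional to time: c = 0.42/8, b = 0.

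**4. Precision.** With half the dyads allocated CSP, the variance inflation is 1 + m²/(2s²) = 1 + 64/18 = 4.6, so the SE is multiplied by about 2.1: 0.112 × 2.1 = 0.24. Cutting time off at 0 and 12 narrows its spread, and simulation (4,000 replicates per scenario) gives 0.255.

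**5. Simulated results for contrast A, true effect 0.42**

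| Scenario | Mean estimate | Power |
|---|---|---|
| Covariate left out | 0.42 | about 96% |
| In model, benefit not time-dependent | 0.42 | about 38% |
| In model, half time-dependent | 0.21 | 13–14% |
| In model, fully time-dependent | about 0 | 5% |

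Check on the second row: 0.42/0.255 = 1.65; 1.65 − 1.96 = −0.31; power 38%.

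**6. Duration related to prognosis.** The residual SD is √0.75 = 0.866. A correlation of +0.3 between time and the outcome residual gives c = 0.3 × 0.866/3 = 0.087, so b = 0.42 − 8 × 0.087 = −0.28. A correlation of −0.3 gives 0.42 + 0.70 = 1.12. Simulation with the cut-off gives about −0.3 and +1.15.

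**7. Other durations, capped at the planned 10 months.** With mean 7.7 and SD 2.1, or mean 6.8 and SD 2.6, the variance inflation is 8.0 or 4.5. Power with constant benefit is 26% or 43%. With fully time-dependent benefit the estimate is again about zero and rejection 5%.

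**8. The other contrasts.** Under the step 4 durations, the RYCT SE is 0.119 with or without the covariate, and the interaction SE is 0.237 without and 0.238 with it; both estimates stay at their true values. The reason is that both CSP differences, with and without RYCT, lose the same c·m, which cancels in the interaction when mean time is similar in the CSP and combined arms.

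**The case against.** The strongest reply is that the damage depends on coding the article does not state. If time is centred within the CSP arms, the CSP coefficient returns to 0.42 with an SE of about 0.11 to 0.12 and power of about 94% or more, in every scenario above. Such detail often sits in a full analysis plan, which is not shown. This stands as a limit on the figures, which are illustrations. It does not remove the point: the article names the covariate and states nothing that makes it harmless.

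The planned mixed models would also give a 12-month CSP effect without this covariate. That mitigates, but nothing makes them replace the analysis of covariance. Nor does the article call that model primary; its standing is inferred from 12 months being the main endpoint.

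Three stronger readings are tempting, and the documents do not support them.

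- A reader might infer that contrast A would be biased towards zero or reversed. The direction is unknown: it depends on whether carers who fare better or worse stay longer, and the article does not say. If duration affects neither benefit nor prognosis, there is no bias, only lost precision.
- A reader might infer that the interaction and RYCT tests are damaged because they share the model. Step 8 shows essentially no effect when time on CSP is similar in the two CSP arms.
- A reader might call this a flat contradiction of analysis by allocation. Dyads are still compared in their allocated groups and nobody is reclassified. The conflict is over what the adjusted coefficient estimates.

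**Conclusion.** The point holds for contrast A. As written, the 12-month model conditions on exposure to one of the randomised treatments. With raw months and zero outside the CSP arms, its CSP coefficient is a difference extrapolated to zero months, which equals the effect of allocation only if duration is related to neither benefit nor prognosis. Even in that best case the SE roughly doubles, from 0.11 to about 0.26, and power drops from about 96% to about 38% under the main assumptions (26% to 43% under the alternatives). If benefit is fully proportional to time, the test has no power beyond its 5% error rate.

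These sizes rest on assumed durations, an assumed baseline correlation of 0.5 and zero coding without centring. They also come from ordinary regression without the multi-level terms. That the covariate is a post-randomisation variable rests on none of these assumptions; it follows from the timing in Design and Randomisation.

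**What to change.** Delete length of time on CSP from the 12-month allocation model. Keep baseline outcome and the stratification factors, locality and dyad relationship. Use time on CSP only in a separate secondary analysis, labelled as an exposure analysis and not as the effect of allocation.

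If the covariate was meant to deal with the staggered second randomisation, it is the wrong variable, because that wait occurs in all four arms. Use the interval between the two randomisations where it is recorded. The article does not say that both dates are stored, and a dyad that leaves before the second randomisation has no such interval, so the plan should say how those dyads are handled.

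The main change is one line of analysis wording. It needs no new data and no change to the design or sample size.

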**Figure 1 F1:**
[figure not shown]
**Flow diagram of the SHIELD CSP-RYCT trial**. A two-stage sequential dynamic algorithm is used in which participants are first randomised individually to CSP or TAU and later on a group basis to RYCT or TAU.

The design tests three null hypotheses:

i) There is no effect of CSP compared with TAU

ii) There is no effect of RYCT compared with TAU

iii) There is no interaction between RYCT and CSP

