### Sample size

We based sample size calculations on the BECCA [12] and REMCARE [18] trials. These predicted effect sizes, defined as average effect per participant divided by population standard deviation, of 0.42 for CSP and 0.35 for RYCT. In a 2 × 2 factorial design using a 2:1 allocation ratio in favour of groups receiving RYCT, a completed sample of 240 dyads would yield power of more than 90% to detect both main effects using a significance level of 5%. This design would also yield power of more than 80% to detect interaction between CSP and RYCT equivalent to an effect size of 0.4, using an analogous definition. As both the REMCARE trial platform and BECCA retained some 80% of participants, we aim to recruit 300 dyads in 13 rounds of 24 dyads to yield a final sample of 240 dyads.

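### Contrast C, the interaction test, is not tied to a model with both main effects; if its arms are simply pooled under 1:2:1:2 allocation it carries one third of the CSP effect

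*Protocol article*

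**What the plan says.** The Design section sets out three null hypotheses, the third being "There is no interaction between RYCT and CSP". Effectiveness analysis repeats the aim as "C. CSP and RYCT interacted in their effects on these outcomes". It then specifies a multi-level analysis of covariance on the 12-month outcome, with the baseline value and length of time on CSP as covariates, and lists three group comparisons. A sets the two arms with CSP against the two without. B does the same for RYCT. The third is given as "C) combined and TAU groups with CSP and RYCT groups".

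A later sentence treats the CSP and RYCT factors as fixed effects. It comes after the sentence that introduces the longitudinal mixed models, and it names no interaction term.

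Under Design, "we randomise between TAU, RYCT, CSP and combined in the proportions 1:2:1:2"; the Randomisation section gives the same ratio. Under Sample size, "a completed sample of 240 dyads would yield power of more than 90% to detect both main effects", with predicted effects "of 0.42 for CSP and 0.35 for RYCT". The same section claims more than 80% power for an interaction equivalent to an effect size of 0.4.

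**The concern.** Setting one diagonal pair of arms against the other isolates the interaction if the four arm means are weighted equally, or if both main effects are in the model. With unequal arms and simple pooling it does neither. RYCT arms are twice the size of the others, so two thirds of the combined + TAU pool has received CSP, against one third of the CSP + RYCT pool. Part of any CSP benefit would then appear as interaction.

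At stake is one of the three hypotheses the trial is designed to test. A working CSP could produce an apparent synergy that does not exist, or hide a real negative interaction. Either would also affect how A and B are read. A and B do not have this fault, so the same style of wording is harmless in two comparisons and matters only in the third.

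**Working it through.** **Inputs.** From the protocol: 240 completed dyads, ratio 1:2:1:2, CSP effect 0.42 SD, RYCT effect 0.35 SD, 5% significance level. Assumed: two-sided test (sidedness is not stated), equal retention across arms, SD 1, independent dyads. The completed arms are then TAU 40, RYCT 80, CSP 40, combined 80.

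**1. The plan's interaction power (more than 80% at 0.4).** Normal approximation:
- Equal-weight half contrast, 0.5 x (combined + TAU - CSP - RYCT): SE = 0.5 x sqrt(1/40 + 1/80 + 1/40 + 1/80) = 0.137; power 83.2%.
- Pooled arms, 120 against 120: SE = sqrt(2/120) = 0.129; power 87.3%.
- Full difference of differences of 0.4: SE = 0.274; power 30.9%.

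The first two meet the stated figure. This points to the half-contrast scale, but it does not separate equal weighting from pooling.

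**2. What pooled C estimates.** Let the arm means be TAU 0, CSP a, RYCT b, combined a + b + i.
- Combined + TAU: 80(a + b + i)/120 = (2/3)(a + b + i).
- CSP + RYCT: (40a + 80b)/120 = a/3 + 2b/3.
- Difference: a/3 + 2i/3.

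RYCT cancels; one third of the CSP effect stays. With the CSP main effect M = a + i/2, the same quantity is i/2 + M/3: the half contrast plus one third of the CSP main effect.

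**3. A and B for comparison.** Pooled A is [40a + 80(a + b + i)]/120 - 80b/120 = a + 2i/3. Pooled B is [80b + 80(a + b + i)]/160 - 40a/80 = b + i/2. Neither carries the other factor's effect.

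**4. Size when there is no interaction (a = 0.42, i = 0), time covariate left out.**
- Expectation 0.42/3 = 0.14 SD; 0.14/0.129 = 1.08 standard errors.
- Rejection at 5%: 19.2% by formula, 17.0% in 20,000 simulated trials (the simulated residual also contains the differences between arms).
- With an assumed baseline correlation of 0.5: SE = 0.129 x sqrt(1 - 0.25) = 0.112; rejection 24.0% by formula, 22.0% simulated.

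**5. Masking.** a/3 + 2i/3 = 0 when i = -a/2 = -0.21 SD. An interaction of that size has zero expectation in pooled C.

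**6. Effect of the time covariate.** Pooled C was simulated without main effects but with time on CSP, set to zero in arms without CSP (4,000 trials per setting; times are assumptions):
- mean 10 months, SD 2: bias about 0.01, rejection 4% to 5%;
- mean 8, SD 3: bias about 0.03, rejection 5% to 6%;
- mean 6, SD 4: bias about 0.06, rejection 7% to 8%.

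**7. Both main effects in the model.** In the 20,000 simulated trials the mean of C is 0.00 to two decimals and rejection is 5.1%. Power at 0.4 is the 83.2% of step 1.

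**The case against.** The strongest reply is that A, B and C are the three usual +1/-1 contrasts of a 2 x 2 factorial, and that combined and TAU against CSP and RYCT is the ordinary verbal description of the product term. Fitted together, C is the interaction at any allocation ratio. The stated purpose and the null hypothesis both say interaction, and the factors are called fixed effects in the same section. This stands as far as it goes. A reader might infer that C is simply not a test of interaction, and the article does not support that: it leaves open whether the arms are pooled or the three contrasts share a model.

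A reader might also take the power claim as evidence that a two-group comparison was planned. It is not, because equal weighting (83%) and pooling (87%) both exceed 80%.

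Third, the 17% to 24% error rates omit a covariate that the article names. This is also correct: if time on CSP is zero where CSP was not allocated, most of the leak goes. That protection is accidental, though. It depends on a post-randomisation variable whose coding is not stated, and it works by absorbing the CSP effect that A is meant to estimate.

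Finally, a condensed article may leave model coding to an analysis plan that is not shown. But the article does state the comparison for C, and that statement is open to a biased reading under its own allocation ratio.

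**Conclusion.** The point holds conditionally. If the arms are pooled literally, C is wrong as written: it estimates a/3 + 2i/3, with an expectation of 0.14 SD at a CSP effect of 0.42 and no interaction. If C was meant as the product term alongside both main effects, the test is sound and only the wording needs tightening.

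The type I error of about 17% to 24% applies only to pooled arms without the time covariate; its upper part assumes a baseline correlation of 0.5. A reader might take it as the error rate of the planned analysis. The article does not support that, since with the time covariate coded zero outside CSP the rate is about 4% to 8% under the assumed times. All figures rest on two-sided 5% tests, arms of 40/80/40/80 and no clustering.

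The article does not settle which reading applies, so this is not a high-confidence essential correction. It is worth making because the comparison as worded is not a clean test of the third null hypothesis.

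**What to change.** State that C is the CSP x RYCT product term in a single 12-month model that also contains the CSP and RYCT main effects. This is equivalent to (combined - RYCT) - (CSP - TAU) with the four arm means weighted equally. Report it with a 95% confidence interval, and say whether it is given as the full difference of differences or as half of it, since the power claim at 0.4 reproduces on the half scale. A and B need no change on this account.

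The cost is one sentence and no new data. Type I error is about 5%, and power at 0.4 on the half-contrast scale is 83%, still above the stated 80%.

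### The supplementary mixed models for 5 and 12 months list their fixed effects without the baseline outcome, which the 12-month ANCOVA includes

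*Protocol article*

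**What the plan says.** The Design section of the protocol article fixes three assessment times and the main endpoint: "We collect data at baseline (post-consent, pre-randomisation), and 5 and 12 months after the first randomisation, with the main endpoint at 12 months". A pre-randomisation measurement is therefore part of the data collection.

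The Effectiveness analysis section then describes two models.

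- **12-month comparison:** the model is given in these words: "multi-level analysis of covariance with outcome at 12 months after initial randomisation as dependent variable and 'outcome' at baseline and length of time on CSP". The last two terms are adjusted for, so baseline is named here.
- **Longitudinal comparison:** "We shall also use linear mixed models to study longitudinal effects at 5 and 12 months". The next two sentences sort the terms. Fixed: "We shall treat RYCT versus TAU and CSP versus TAU as fixed effects, together with gender and dyad relationship". Random: "We shall treat the effects of locality (including personnel) and time as random effects and assess the covariance structure of this".

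The baseline outcome appears in neither of these two sentences. The section does not say that it is excluded, and it does not say that it carries over from the ANCOVA.

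**The concern.** The mixed model is the only effectiveness analysis described in that section that models the 5-month outcomes. If an analyst fits it from the listed terms, it compares follow-up scores adjusted for gender, dyad relationship and locality, but not for the participant's own starting score. Three things follow.

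1. The standard errors for CSP and RYCT are larger than the collected data require.
2. Part of any chance baseline difference between arms stays in the estimate.
3. The 12-month effect from the mixed model can differ from that of the ANCOVA simply because the two adjust for different things, and a reader could not tell this from a substantive discrepancy.

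**Working it through.** **Inputs from the protocol article.** Completed sample 240 dyads, effect sizes 0.42 SD (CSP) and 0.35 SD (RYCT), 5% significance (Sample size). Allocation "we randomise between TAU, RYCT, CSP and combined in the proportions 1:2:1:2" (Design), so the factorial margins at 240 are CSP 120 v 120 and RYCT 160 v 80.

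**Assumptions.** Two-sided test, independent dyads, SD = 1, and a baseline to follow-up correlation r of 0.3, 0.5 or 0.7. The document gives no value for r.

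**Formulae.** Unadjusted SE = √(1/n₁ + 1/n₂). Baseline-adjusted SE = √(1 − r²) × unadjusted SE. Power ≈ Φ(d/SE − 1.96).

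**Step 1: the plan's own figure.** The Sample size section states more than 90% power for both main effects.

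- CSP: SE = √(1/120 + 1/120) = 0.129; 0.42/0.129 = 3.25; power 90.2%. This reproduces.
- RYCT: SE = √(1/80 + 1/160) = 0.137; 0.35/0.137 = 2.56; power 72.4%. This does not reproduce without adjustment. Reaching 90% would need baseline adjustment with r of about 0.615.

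The RYCT shortfall is a separate matter. It is noted here only because it shows that RYCT has little precision to spare.

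**Step 2: effect of adding baseline, at a single visit.**

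| r | √(1 − r²) | SE excess if omitted | 240(1 − r²) | RYCT power | CSP power |
|---|---|---|---|---|---|
| none | 1 | – | – | 72.4% | 90.2% |
| 0.3 | 0.954 | 4.8% | 218 | 76.4% | 92.7% |
| 0.5 | 0.866 | 15.5% | 180 | 83.9% | 96.4% |
| 0.7 | 0.714 | 40% | 122 | 94.7% | 99.5% |

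The fourth column is the number of adjusted dyads that carry the same information as 240 unadjusted ones.

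**Step 3: disagreement with the ANCOVA.** A baseline imbalance of 0.1 SD moves the unadjusted estimate by 0.1 × r, that is 0.03, 0.05 or 0.07 SD. Over randomisations, the SD of the gap between unadjusted and adjusted estimates is r × unadjusted SE:

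- RYCT: 0.041, 0.068 and 0.096
- CSP: 0.039, 0.065 and 0.090

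At r = 0.5 the RYCT gap has an SD of about one-fifth of the 0.35 target (0.068/0.35 = 0.19).

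**Step 4: bias.** In 4,000 simulated trials at each r, both estimators centred on the true effects. At r = 0.5 the means were 0.421 unadjusted and 0.422 adjusted for CSP, and 0.349 and 0.348 for RYCT. Only the spread differed: 0.129 v 0.113 for CSP and 0.137 v 0.119 for RYCT.

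**Step 5: could baseline enter as a response instead?** The list has no treatment-by-time term. If baseline were a third response, each listed treatment effect would average over three visits, one of which has an expected difference of zero. With equal weights and a constant effect at both follow-ups, it shrinks to two-thirds: 0.35 to 0.23 and 0.42 to 0.28.

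**The case against.** The strongest reply is that the list is visibly partial, so absence from it does not show a decision to exclude. The interaction tested in comparison C is missing too. So is the interviewers' perceived allocation, which the Blinding section says will be a covariate. The section also uses two vocabularies: baseline is a covariate, while treatments, gender and locality are effects, so the quoted sentence may only be sorting factors into fixed and random. It may even be completing the ANCOVA, which is called multi-level but is otherwise given no levels. The complete covariate list of an additional model may sit in an analysis plan that is not shown.

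Much of this stands. The document does not support reading the list as a deliberate exclusion of baseline. But none of these readings puts baseline into the mixed model. If the list completes the ANCOVA, the mixed model has no stated covariates at all. If baseline is a response, the listed effects are diluted (Step 5). The article did choose to spell out this model's terms, down to gender, and left out the score it had named for the model just before.

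It is also fair that every power figure rests on an assumed r, and that the comparison is with no adjustment at all. The listed model already adjusts for gender, dyad relationship and locality, so the further gain from baseline would be slightly smaller if these explain some of the same variance.

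**Conclusion.** The point holds as a correctable gap in a supplementary analysis. As listed, the 5- and 12-month mixed models omit a baseline score that the trial collects and that the ANCOVA uses. The cost in precision is small at r = 0.3 (RYCT power lower by 4 points, CSP by 2 to 3). It is material at r = 0.5 (about 12 and 6 points) and large for RYCT at r = 0.7 (about 22 points, against 9 for CSP). These figures assume a single visit, 240 completers, independent dyads and a two-sided 5% test.

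A reader might infer three stronger things, and the document supports none of them:

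- **That the main result is compromised.** The main endpoint is at 12 months and its ANCOVA is baseline-adjusted.
- **That the longitudinal estimates are biased.** Chance imbalance adds variance, and only a fraction r of it reaches the estimate in a given trial. Over repeated randomisation there is no bias.
- **That the loss should be judged on the mean of the two visits.** With equal correlation of 0.5 between all visits, adding baseline would raise RYCT power for that mean from 84% to 95%. The arithmetic is correct, but the plan does not name this average as a quantity to be estimated and does not power for it.

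**What to change.** In the Effectiveness analysis section, add the baseline value of the outcome to the fixed effects of the linear mixed models, and state that only the 5- and 12-month outcomes are responses. A possible wording: the fixed effects are RYCT, CSP, the baseline value of the outcome, gender and dyad relationship. The longitudinal model then has the same baseline adjustment as the 12-month ANCOVA. If the full analysis plan already says this, the article need only be brought into line with it. The cost is one phrase: the baseline data are already collected, and no further participants or visits are needed.
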